### Ethics and dissemination

Written consent is sought from all participants. For those under legal guardianship, consent is also sought from the guardian. The patients’ identity on the questionnaires will be pseudonymised by the recruiting practice. Only the pseudonymised filled-out questionnaires will be sent to the study centre. Thus, there is no direct contact between patients and researchers. The Research Ethics Committee of the Lower Saxony Medical Association approved the study (Ärztekammer Niedersachsen BO/03/2011). It is compliant with the Helsinki Declaration. The reporting of the study will be in accordance with standards of the CONSORT extension for pragmatic trials and the TREND statement
[30,31].

## Discussion

There are many challenges confronting this pragmatic study on the effectiveness and efficiency of this assertive outreach (AO) model in rural areas of Lower Saxony in Germany:

### Researching a real life implemented intervention

While it is common in trials that extra time is planned for the tasks related to research, this is not the case in this pragmatic study evaluating a real-life implemented intervention. All service providers participating in the study do so voluntarily and in addition to their daily routine and regular professional obligations. So first of all, office-based psychiatrists have to be convinced to participate in the study. Then, they have to recruit patients for participating in the study, seek their consent, hand them questionnaires, fill in questionnaires themselves and send pseudonymised data to the study centre. To motivate the psychiatrists to do all these additional tasks in conjunction with the study, they are offered quite a generous honorarium. Further, all practices will have a personal researcher assigned who will support them with advice during the whole process of the study. In addition, the study protocol seeks to keep extra work for service providers to a minimum. Thus, most questionnaires are filled out by the patients themselves. The questionnaire on use of services needs to be filled out by the practice assistant together with the patient.

Despite the challenge of motivating office-based psychiatrists to participate in the study and of keeping their motivation high during the course of the study, a pragmatic study has advantages over an experimental trial. While a trial is always a kind of in vitro artificial situation, a pragmatic study deals with the real life conditions of the health system. This implies that patients appear with the average mix of co-morbidities. Also, health care providers have, on average, a mixture of qualifications compared with top-level trained specialists in academic centres. They all operate within the constraints of the health system. These real life conditions may make research more difficult however, they also increase external validity
[32]. In case that a real life study succeeds in showing the effectiveness and efficiency of an intervention, the likelihood increases that this intervention does in fact work
[33]. On the other hand, the validity of the results is impaired by possible selection biases, as in the study presented here, real randomisation was not possible. At the same time, the – possibly effective – intervention is likely to be more sustainable than interventions that are only implemented in the context of a trial. Many home treatment interventions that were implemented in the context of a trial were not maintained for long beyond the trial
[34].

### Researching severely ill people

AO is meant to be an intervention for the more severely mentally ill. To assure this, the Global Assessment of Functioning Scale (GAF) is used as an inclusion criterion. This means that patients in this study experience at least moderate to severe problems in social or vocational functioning. We expect many patients to be much more impaired than GAF 60. As our pre-tests showed, filling out a questionnaire can be quite challenging to such impaired patients. To enable a broad participation also for more severely ill persons, we had to keep the questionnaires as lean as possible. This implies that we preferred shorter, simplified questions over the original longer ones. We boiled down quality of life to one question rating life satisfaction on an 11 point scale
[16] as well as restricted the alcohol and drug use scale to two introductory questions referring to the quantity of alcohol and drug intake.

### Controlling for TAU

Whether an intervention that changes the modes of services provision such as case management is effective or not, is not only related to the strength and quality of the intervention, but also the quality of TAU to which the intervention is compared is decisive
[35,36]. This study will assess the use of services in intervention and TAU condition every three months by means of the Client Sociodemographic and Service Receipt Inventory (CSSRI). Thereby, we will be able to describe in detail characteristics and differences in the care that patients receive in the intervention and TAU group. This will enable us to interpret our outcome findings by considering the process of care.

### Bias

We aim to recruit equal numbers of patients receiving the intervention and of controls from the same psychiatrist. Thus, possible bias in respect to context variables will be minimised. Further, the relatively high number of participating psychiatrists should eliminate data distortion due to different physician-patient interaction styles.

The quasi-experimental design that distinguishes participants by their affiliation to a specific health insurance company and thus, their eligibility for AO, can limit the study validity. The data from the study will show whether our assumption is true that schizophrenic patients in different health insurance companies are more or less equal in terms of socio-economic and health status.

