### Recruitment

Patients will be recruited in the practices of office-based psychiatrists who provide AO. Recruitment will be done by the treating psychiatrist. Unfortunately, we were not successful in convincing the attending psychiatrists to support “real” randomisation of patients receiving AO or those receiving TAU. “Real” randomisation would have meant that the office-based psychiatrists would lose 50% of the extra money they receive from health insurance companies when providing AO. Therefore, a quasi-experimental design will be used instead. As patients allocated to receive the intervention all those patients are considered, who are insured by a health insurance that reimburses AO, and who in fact receive AO. All patients who - due to their health insurance affiliation - are not eligible for AO are considered to be controls. We assume that the affiliation with a specific statutory health insurance company is more or less random. Choice of health insurance company is free, all statutory health insurance companies offer approximately the same services, cost the same and are obliged to insure people regardless of their health and financial status. Even if there might be some differences in social status between the members of different health insurance companies, these differences are most likely obliterated by the social consequences of suffering from schizophrenia.

In this quasi-experimental design, all attending practices recruit the same number of patients receiving the intervention and of patients being controls. An honorarium of 150€ will be paid to the practice per assessment and patient. Patients will receive an honorarium of 20€ per assessment.

Eligibility criteria are: being at least 18 years of age, suffering from schizophrenia (ICD-10 F 20) as diagnosed clinically by the treating psychiatrist, having a maximum score of 60 on the Global Assessment of Functioning Scale (GAF)
[14] and being cognitively and linguistically able to fill out the patient questionnaire.

Recruitment is planned to take a year.

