### Sample size

Previous studies performed in Leipzig, Germany, have shown a mean number of days spent in psychiatric inpatient care by schizophrenic patients of 47 (SD 83)
[27]. Further, studies estimated the mean decrease of inpatient days that can be expected from interventions to be 40%
[28]. According to Hedeker and colleagues (1999), a baseline sample size of 242 participants in each group would be required to detect a small effect size of 0.2 with a power of 0.80 at a two-tailed significance level of 0.05
[29].

Previous studies have shown that 20% of patients cannot be traced for follow-up or do not return questionnaires over a 12-month survey period
[27].We aim to reduce drop-out numbers by keeping records of patients' telephone contact details as well as secondary contact names and addresses at the practices of the attending psychiatrists. If patients fail to return for assessment to the attending practice, they are contacted by phone and asked whether they want to continue with the study. This way, we hope to keep the number of drop-outs at a rate of 10%. Thus, the total number of participants to be initially recruited will be 268 patients per group or 536 in total.

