### Statistical analysis

We will analyse data using per-protocol analysis, considering only those patients who successfully completed the study, as well as using an intention-to-treat approach. Thereby we would also consider those patients who dropped out of the study or changed their originally allocated group.

We will report baseline demographic and clinical characteristics for each study condition and test for baseline equivalence using parametric and non-parametric test as appropriate. If necessary, we will control for baseline differences. Missing data will be analysed.

Longitudinal data will be analysed using standard models for repeated measures including multivariate mixed effects analysis of variance, random effects and generalized estimating equation (GEE) models, as appropriate.

Whenever possible, measures of "practical relevance" such as proportion of explained variance, accuracy of prediction, or effect size will be reported. Statistical analyses will be performed using standard software packages (SPSS, STATA).

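### The number of psychiatrists does not eliminate practice effects: balance within practice or conditioning on practice does, and no stated analysis names practice

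*Protocol article*

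**What the plan says.** The Recruitment section states that "all attending practices recruit the same number of patients receiving the intervention and of patients being controls". The Bias section presents the same balance as something the study aims for and credits it with minimising bias from context. It then adds a second, separate reason for reassurance: "the relatively high number of participating psychiatrists should eliminate data distortion due to different physician-patient interaction styles".

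The Statistical analysis section plans "standard models for repeated measures including multivariate mixed effects analysis of variance, random effects and generalized estimating equation (GEE) models, as appropriate" for the longitudinal data, with control for baseline differences if needed. It plans both a completers-only (per-protocol) analysis and an intention-to-treat analysis. Neither practice nor psychiatrist is named there as a stratum, a model term or a cluster. The Sample size section also makes no reference to practice.

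The Background says that about 40 practices have joined the management association. The number that will recruit is not given.

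**The concern.** The design uses practice as its balancing factor, because AO and TAU patients are to come in equal numbers from the same psychiatrist. What protects the comparison is that balance, or an analysis that compares patients within practice. The number of practices does neither. With many practices the random part of the differences shrinks, but a systematic link between a practice's outcomes and its share of AO patients remains however many there are.

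This matters more here than in a randomised trial. The treating psychiatrist recruits, and group follows insurance affiliation. Only about one third of the area's population is with the two contracting insurers (Background), and AO patients must also consent to AO, so equal numbers may be hard to reach in some practices. One analysis keeps completers only. AO is also delivered by each practice with nursing services, so its effect may differ between practices, which a standard error that ignores practice would miss.

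**Working it through.** **Inputs from the documents.** 242 per group before drop-out, 268 per group (536 in total) recruited, 10% drop-out hoped for and 20% seen before. Inpatient days have mean 47 and SD 83, with an expected 40% reduction: 0.4 × 47 = 18.8 days, or 18.8/83 = 0.23 SD.

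**Assumptions, not in the documents.** Practice ICC 0.02 to 0.10; 40 recruiting practices (the association's membership); the spread of the AO share and of the AO effect as given below; a difference in means on a roughly normal scale.

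**The plan's own figure.** 242/0.9 = 268.9, against the stated 268, so the drop-out step reproduces to rounding. The 242 itself does not follow from an effect size of 0.2 "with a power of 0.80 at a two-tailed significance level of 0.05" by the plain two-group formula, which gives 393. A repeated-measures correlation that the article does not state could explain it. That is a separate matter, and 242 is taken as given here. Average practice size is 536/40 = 13.4 patients, or 6.7 per group.

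**1. Exact 1:1 balance.** Practice effects cancel. In 4,000 simulated trials per setting (40 practices of 12 patients, no treatment effect), estimates with and without practice were identical and unbiased. Conditioning multiplies the variance by (1 − ICC). At ICC 0.05, 242 × 0.95 = 230 per group would suffice. The unconditioned test has true size 2[1 − Φ(1.96/√0.95)] = 0.044, which is conservative.

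**2. Imbalance unrelated to practice outcome.** With AO shares between 30% and 70% at random, the simulation showed no bias and a type I error of about 0.05.

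**3. AO share related to practice outcome.** If the share has mean 0.5 and SD s, and its correlation with the practice mean is r, the pooled difference is biased by 4 × s × r × √ICC (in SD). The naive standard error is √(4/484) = 0.091. With s = 0.10 and r = 1:

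| ICC | Bias, formula (SD) | × 83 (days) | Type I error, formula | Simulated bias (SD) | Simulated type I error |
|---|---|---|---|---|---|
| 0.02 | 0.057 | 4.7 | 0.10 | 0.054 | 0.09 |
| 0.05 | 0.089 | 7.4 | 0.17 | 0.089 | 0.16 |
| 0.10 | 0.126 | 10.5 | 0.29 | 0.124 | 0.26 |

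Against 18.8 days this is roughly a quarter to a half of the planned effect. With practice indicators the bias was about 0 and the type I error 0.04 to 0.05. The bias is proportional to s and to r: halving either halves it. At ICC 0.05 in a similar simulation, the pooled bias was 0.085 SD, and a random practice intercept still left 0.049.

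**4. AO effect varying between practices with SD τ.** The ratio of true to naive variance is R = 1 − ICC + (τ²/K)/(2/242), and the test size is 2[1 − Φ(1.96/√R)]. With K = 40 practices:
- ICC 0: R = 1.030, 1.121 and 1.272 for τ = 0.1, 0.2 and 0.3, giving test sizes of 0.053, 0.064 and 0.082.
- ICC 0.05: R = 0.980, 1.071 and 1.222, giving 0.048, 0.058 and 0.076.

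With K = 20 and τ = 0.2 at ICC 0, R = 1 + 0.002 × 121 = 1.242 and the size is 0.079, against 0.064 with 40.

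**The case against.** The strongest reply is that the design already does the work. Under the stated 1:1 recruitment the pooled estimate is unbiased and its test errs on the safe side. That is right. A reader might infer that the Bias sentence can hold only if practice is in the model. The documents do not support that, because exact balance suffices.

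A reader might also infer that drop-out by itself will bias the comparison. It need not, as step 2 shows. Its reach is also limited. If the planned 10% loss fell wholly in one group, the average practice would end at 6.7 against 6.7 − 1.34 = 5.36, or 1.25:1. At 20% it would be 6.7 against 4.02, or 1.67:1. A share SD of 10 points fully aligned with outcome is therefore a demanding scenario that would need recruitment shortfall too, and the documents give no evidence of such alignment.

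An effect SD of 0.2 to 0.3 is likewise about as large as the planned effect of 0.23. It would imply AO doing harm in Φ(−0.23/0.2) = 13% to Φ(−0.23/0.3) = 23% of practices, so the upper end is pessimistic.

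Finally, it is tempting to say that the plan excludes practice. It does not: random-effects and GEE models are allowed as appropriate with the grouping left open, and an analysis plan may name practice. The article also admits possible selection bias in its Discussion.

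These points limit the size of the problem. They do not rescue the sentence, which gives a wrong reason for setting practice effects aside.

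**Conclusion.** The concern holds in a limited form. The claim that many psychiatrists should eliminate distortion is wrong about the mechanism, in a non-randomised study whose within-practice balance is stated as fact in one section and as an aim in another. No stated analysis names the factor on which the design balances.

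If balance is exact, the cost is small: about 5% of precision at ICC 0.05. If the AO share follows practice outcome, the bias could reach about 0.06 to 0.12 SD (5 to 10 days) under the full-alignment assumption, and proportionately less under weaker alignment. If AO effects vary between practices, the test is modestly too liberal, at about 0.05 to 0.08 with 40 practices and more with fewer. Participation is voluntary and 40 is the association's membership, so fewer may recruit. The ICC, share SD, alignment, effect SD and number of practices are all assumptions. The direction of each effect does not depend on their exact values.

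**What to change.** In the Statistical analysis section, state that the primary comparison conditions on practice, through practice indicators (fixed effects) or a within-practice contrast. A random intercept alone is not enough, because it leaves roughly half or more of this confounding. Add practice-clustered robust standard errors or a random practice-by-group effect, so that the interval allows for AO working differently between practices. Reword the Bias section to say that balance within practice and adjustment for practice reduce distortion from interaction styles, and drop the appeal to the number of psychiatrists.

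The cost is a few lines of text and no new data, since patients are recruited through their practice. Some degrees of freedom are lost to the indicators (39 for 40 practices), and the interval will be slightly wider if AO effects do vary. Under exact balance and a constant effect, the change lowers the sample size needed.

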## Conclusion

In a mental health system that is as fragmented as the German one, it is crucial to find interventions that bridge some of the fragmentation in service provision. The model of AO that is to be researched in this study presents one possible solution to some of the fragmentation of the system. It is innovative in the context of the existing system. By integrating outpatient psychiatric care with ambulatory nursing services, the model provides an AO-style intervention to the severely mentally ill. The findings from the study, regardless of whether they will support or reject the hypotheses, will be of great use for the further development of integrated care and home care in Germany’s mental health system, as well as in other similar health systems.

## Endnotes

^a^There are 146 statutory health insurance companies in Germany, insuring approximately 90% of the population. AOK and TK are among the larger health insurance companies. AOK Lower-Saxony insures more than one quarter of the population in Lower-Saxony, TK insures close to one tenth of the population in Germany. While AOK insured traditionally have a lower socioeconomic status, TK insured come from an academic and middle class background. Probable social disparities between the insured populations of health insurances companies are originated in former times, when health insurance affiliation was bound to the workplace. For more than 15 years now, choice of health insurance has been free and social disparities between the insured populations of the health insurance companies are levelling out.
